### Ethics

The study has been approved by the Institute Research Board Ethics Committee (approval numbers: AIIMSA2969/03.01.2025, RP-46/25, OP-16/02.05.25, and OP-18/05.12.2025) and has been prospectively registered at ClinicalTrials.gov (CTRI/2025/03/081645). Written informed consent will be obtained from all participants prior to enrollment, and participants may withdraw their consent at any time without consequence. A participant information sheet (PIS) in the local vernacular language will be provided to all eligible patients before randomization. The PIS document will detail the purpose of the study, measurements, procedures involved, and the risks and benefits of participation in the trial. PIS and PICF details given in S2 Annexure.

### Data and protocol availability

The data underlying this study include sensitive clinical and personal information about individuals living with HIV. Due to the highly confidential nature of HIV status and the risk of participant identification, ethical restrictions prevent public sharing of the dataset. De-identified data may be made available to qualified researchers upon reasonable request. Data requests can be directed to the Institutional Ethics Committee, All India Institute of Medical Sciences (AIIMS), New Delhi, which is responsible for reviewing and approving access to confidential data. The data will be kept at health Centre for ten years after the data collection. No images or any personal or clinical details about participants are included in this report, and none will be included in future publications.

### Adverse reactions monitoring

Throughout the study, each participant will be closely monitored and will be recorded for any adverse reactions that might result from the yoga intervention, any signs of disease progression, any ART regimen/ dose adjustments, or treatment interruptions (toxicity, intolerance, adherence issues). All reported or observed events will be clinically reviewed by the clinician to determine causality—classified as ART-related, intervention-related (yoga), related to HIV disease progression, or unrelated. In the event of adverse reactions or disease progression, the treating physician will use clinical judgment and safety factors to determine whether a participant should remain in the study. Participants will receive proper medical attention and any required modifications to their yoga intervention in case of disease progression or adverse reactions. To ensure the safety and well-being of every participant in the trial, any adverse occurrences will be recorded, submitted to the ethics committee, and examined.

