13.	Protocol deviations	The program will be tailored to the conditions, characteristics, preferences, progression, and improvements of the participant. Modifications will be made and reported based on the participant’s condition or in case of disease progression during the trial (if any).
14.A	How well – Plan	**Compliance and adherence:** To be compliant with the yoga intervention, every participant must attend at least 27 out of the 36 sessions (75%) Participants will be considered adherent if they attend ≥75% of the scheduled supervised yoga sessions, and the prescribed home-practice minutes as recorded in standardized log-book diaries.
14.B	How well – Actual	Adherence and compliance will be evaluated using class attendance logs, self-reported home practice using log-book, and telephonic calls (every 15 days). Participant’s partners will be invited to join the sessions to enhance their adherence.
15.A	Harms – Plan	Throughout the study, each participant will be closely monitored for any adverse reactions that might result from the yoga intervention, or ART medication and for any signs of disease progression. In the event of adverse reactions or disease progression, the treating physician will use clinical judgement and safety factors to determine whether a participant should continue in the study. Participants will receive proper medical attention and any necessary modifications to the yoga intervention will be implemented in response to disease progression or adverse reactions.
15.B	Harms – Actual	To ensure the safety and wellbeing of every participant in the trial, any adverse occurrences will be recorded, submitted to the ethics committee, and examined.

Detailed description of the yoga intervention using the TIDieR-Rehab (Template for Intervention Description and Replication for Rehabilitation) checklist.

Abbreviations: ART = Antiretroviral therapy; PLHIV = People living with HIV; RPE = Rating of Perceived Exertion; CIMR = Centre for Integrative Medicine and Research.

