### Control group

The control group will be advised to continue standard medical treatment for the same duration, along with 12 weeks of moderate-to-intensity walking (prescribed brisk walk). The duration of prescribed brisk walk will be at least practiced for a duration of 60 minutes, 3 times/week, divided into three phases: 8-minutes warm-up, 20–25 minutes of brisk walking, and followed by a 15 minutes cool-down and supine rest. Providing moderate-to-intensity walking in the control arm is intended to ensure the candidates’ interest in continuing in the control arm, reduce attrition in the control group, and not limit them from potential risk-reduction practices. Both groups will be given a logbook to track their sleep, physical activity, and medication intake. For more details, see S1 Annexure.

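### The causality categories for adverse events name yoga as the only study activity, so harm from the control arm's prescribed walk cannot be coded to its cause

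*Protocol article*

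**What the plan says.** Under Adverse reactions monitoring, the protocol article says that each participant is monitored and "recorded for any adverse reactions that might result from the yoga intervention". It adds signs of disease progression and changes or interruptions of ART. A clinician then reviews all events and settles the cause, "classified as ART-related, intervention-related (yoga), related to HIV disease progression, or unrelated". The same section provides for changes to the yoga intervention after an adverse reaction or disease progression. It closes by committing to record any adverse occurrence and send it to the ethics committee.

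Table 1, item 15.A, has a similar scope: "any adverse reactions that might result from the yoga intervention, or ART medication". That table describes the yoga arm only.

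Under Control group, controls continue standard treatment "along with 12 weeks of moderate-to-intensity walking (prescribed brisk walk". The walk "will be at least practiced for a duration of 60 minutes, 3 times/week". No section of the article names walking as a possible source of harm.

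**The concern.** The comparator is an active control with an exercise that the trial itself assigns. The causality rule nevertheless has a single study-activity category, and its parenthesis limits that category to yoga. The scope of monitoring (both arms) and the scope of the categories (one arm's activity) do not match.

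Two things are at stake. First, the ethics committee would receive a harm caused by a trial-assigned activity under a label saying that the trial did not cause it. Second, if related events are ever tabulated by arm, the control column is zero whatever happens on the walks.

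**Working it through.** This is mainly a check of categories. Arithmetic enters only as an illustration.

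**Step 1: which category can take a walking injury?** Take a control who falls during the prescribed walk, and go through the four categories.

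| Category in the protocol | Does it fit a walking injury? |
|---|---|
| ART-related | No; a miscoding |
| Intervention-related (yoga) | No; this participant was not assigned yoga |
| HIV disease progression | No; a miscoding |
| Unrelated | The only one left, and false, because the trial assigned the walk |

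The list offers no other category, and the section applies it to all reported or observed events.

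**Step 2: does another section supply the missing category?** No. Adverse reactions monitoring names yoga, disease progression and ART. Table 1, item 15.A, names yoga and ART. Control group describes the walk and a logbook for sleep, physical activity and medication intake, but mentions no harms. Eligibility criteria does treat both activities as possible hazards: it excludes people whose physical disability makes either moderate activity or the yoga practices inadvisable. The causality list carries over only one of the two.

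**Step 3: what is not affected?** The cause assigned to an event does not change whether it is counted. Every participant is monitored and any adverse occurrence is recorded, so a table of all events by arm is free of this coding problem.

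**Step 4: illustration of size.** The arm size comes from Sample size calculation. The stated effect size reproduces as 1.54 / 3.38 = 0.456 (stated as 0.455), and a two-sided t-test at 5% and 80% power needs 76.8, so 77 per group and 154 in total. Allowing for 20% attrition, 154 / 0.80 = 192.5, stated as 192, or 96 per arm. The event risk p is an assumption, taken as equal in both arms, because the documents give none. The expected number coded as activity-related is 96 × p for yoga and 0 for walking.

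| Assumed true risk p | Yoga, as coded | Walking, as coded | Walking, if it could be coded |
|---|---|---|---|
| 2% | 96 × 0.02 = 1.9 | 0 | 1.9 |
| 5% | 96 × 0.05 = 4.8 | 0 | 4.8 |
| 10% | 96 × 0.10 = 9.6 | 0 | 9.6 |

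The zero follows from the category list, not from the assumed rate. I give no false-positive rate, since the plan contains no test of these counts.

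**The case against.** The best defence is that little depends on the label. Adverse events are not a listed outcome, and the statistical sections plan no between-arm safety analysis. A control's fall would still be recorded, reviewed and sent to the ethics committee, and a category marked as yoga makes a zero among controls visibly structural. All of this stands, and it limits the consequence. It does not supply the missing category: the committee would still read the wrong cause.

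Three stronger readings are tempting, and the documents support none of them.

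- *The trial's safety comparison is biased against yoga.* No such comparison is planned. The distortion is confined to a table of attributed events, if one is made.
- *Events are sought more often in the yoga arm.* Table 1, item 14.B, lists "self-reported home practice using log-book, and telephonic calls (every 15 days", but as a means of judging adherence and compliance, in a checklist that covers only yoga. Control-arm detail is deferred to an annexure that is not shown. Both arms have clinical assessment and medical history at baseline and at 3, 6 and 12 months. Unequal contact is therefore not shown.
- *The clinician is improperly unblinded by having to use a yoga category.* The trial is open-label, and blinding is claimed only for the outcome assessor and the statistician. A category for the assigned activity would also require knowing the arm.

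**Conclusion.** The point holds as a gap in a rule that the article itself states, not as detail left to another document. A harm caused by the prescribed walk has no correct code. It would be reported as unrelated or miscoded, and activity-related counts in the control arm are zero by construction.

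The participants who could be mislabelled are those among the 96 controls who have a walking-caused event, not all 96. The contrast of 1.9 to 9.6 events against 0 rests on an assumed equal risk of 2% to 10% and is illustrative only. All-event totals by arm, the efficacy analyses and the sample size are untouched. The change should be made, but the gap does not threaten the trial's main conclusions.

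**What to change.** 1. Replace the yoga-only category with *related to the assigned study activity (yoga or prescribed walking)*, applied by the same rule in both arms.
2. State that adverse reactions to the assigned activity are monitored in both arms, with the same event questions at each shared follow-up visit (3, 6 and 12 months).
3. State that any by-arm safety summary shows all adverse events first, whatever their cause, and related events second.
4. Reconcile the sentences on modifying the yoga intervention after an event (Table 1, item 15.A, and Adverse reactions monitoring) with the description under Control group, since they address only one of the two assigned activities. What the clinical rule should be is for the investigators.

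The cost is a few words in the protocol, one line on the case report form, and slightly more events attributed to the study activity among controls. Trial status puts the start of recruitment in March 2026, so any events already coded under the present list would need their cause reviewed again.

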## Discussion

This randomized controlled trial (RCT) aims to evaluate the efficacy of a structured, validated 12-week yoga intervention that integrates psychological and behavioral components. The life expectancy of PLHIV starting ART has increased markedly over the past 25 years. During this period, the efficacy and side-effect profiles of ART regimens have steadily improved, alongside faster virological suppression and enhanced comorbidity care [37]. Despite these advancements, improved life expectancy must be accompanied by reduced disability and better psychosocial outcomes. Depression is projected to become the leading cause of disability among PLHIV by 2030, contributing significantly to the disease burden through its adverse impact on adherence to treatment, increased mortality and morbidity, rapid disease progression, and several other systemic risk factors [38]. The study is designed with rigorous methodology to generate high-quality evidence on the role of yoga as a complementary therapy in HIV management. Specifically, it will compare yoga to an active control group in terms of its effects on psychological parameters (depression, anxiety, and stress) over a long-term follow-up period. Notably, this will be the first trial to comprehensively assess the pleiotropic effects of yoga on medication adherence, an often overlooked yet critical determinant of sustained virological control.

Previous RCTs have demonstrated that yoga can effectively reduce psychological distress [39,40] and enhance quality of life [41] among individuals living with HIV. Qualitative findings suggest that participants often perceive yoga as a tool for cultivating self-awareness and coping constructively with the physical and emotional challenges of their illness [39]. Building upon this evidence, the present RCT will investigate the physiological mechanisms underlying yoga’s parasympathetic modulation [12] and its potential role in mitigating depression and anxiety by acting on the depression pathways linked to HIV pathophysiology. By examining how yoga influences both psychological and biological mediators of disease, this trial may elucidate mechanisms that can inform refinement of future interventions, enhancing their potency, efficacy, and personalization for maximal benefit in PLHIV.

The present trial possesses several methodological strengths. It employs a randomized design to ensure balanced allocation between groups and to minimize allocation bias and predictability throughout the study. Assessments of outcomes are planned up to one-year post-randomization, enabling the evaluation of both immediate and sustained effects of the yoga intervention. The longer follow-up period will provide valuable insights into the durability of psychological and behavioral benefits over time. Additionally, the use of the TIDieR-Rehab (Template for Intervention Description and Replication for Rehabilitation) checklist ensures comprehensive documentation of the yoga intervention, thereby promoting clarity, transparency, and reproducibility of the study protocol.

A potential limitation of the trial lies in the reliance on self-reported measures for key outcomes such as depression, anxiety, stress, and quality of life. These subjective assessments may introduce recall or response bias; however, standardized and validated instruments will be used to mitigate these effects as far as possible.

If proven effective, the findings from this trial could mark a significant shift in HIV management from a primarily biomedical focus toward a more holistic, patient-centered approach that integrates mental health and overall well-being. Understanding the mechanistic physiological effect of yoga in the disease’s outcome may provide a strong rationale for systematically incorporating structured yoga practices into routine HIV care settings, ultimately enhancing both treatment adherence and quality of life among people living HIV.

### Dissemination

The results of the study will be disseminated with the objective of ensuring the widest possible visibility. All study findings will be published in scientific peer-reviewed journals and presented at scientific conferences.

### Protocol amendments

Any changes to the study protocol will be evaluated and approved by the Institute Research Board Ethics prior to implementation. All pertinent parties, including the Institutional Ethics Committee, CTRI registry, investigators, and, where appropriate, will be promptly informed of any significant protocol amendments. Versions of the updated protocol will be documented and submitted for ethics approval.

### Trial status

Recruitment is planned to begin in March 2026, and data collection is estimated to be completed by March 2028.
